**C.5.a. Rationale:** Survey-based study design allows collection of self-reported information from patients to determine patient-level characteristics associated with barriers and facilitators to adherence to follow-up. We will identify LCS patients using Primordial software and collect survey and EHR data to assess whether poor patient-reported understanding or other factors such as smoking, low SES, minority race, or other comorbidities are associated with poor adherence. Additional data will be retrieved from the EHR including actual radiology reports for LDCT results, recommended follow-up, and provider ordered testing. By recruiting patients who have already had LCS, we can efficiently obtain data for analyses in this 2-year award.

**C.5.b. Overview of study design and procedures:** This is a cross-sectional study. Patients identified from the Primordial LCS registry will be mailed an informed consent and survey to complete. They can choose to either: 1) Complete the paper survey and return it via mail using an enclosed stamped envelope or; 2) Complete the survey via secure on-line access using an identical web-based survey. We will use standard methods to enhance participation rates including a \$10 gift card incentive, reminder/thank-you postcards sent 2 weeks after the initial contact, and second packets with surveys sent to non-responders after 4 weeks.

**C.5.c. Data Collection:** Participants will complete surveys 1-2 months after their planned follow-up per the

| Table 1. Major variables for Aim 1                                    | Source (reference)               |
|-----------------------------------------------------------------------|----------------------------------|
| Demographics: age, sex, race/ethnicity; education, income, zip code   | Survey, Primordial               |
| Employment and health insurance status                                | Survey, Primordial               |
| Tobacco use – current or former, pack years                           | Survey, Primordial               |
| Comorbidities (Charlson comorbidity index)                            | EHR                              |
| Engagement in care (identifies primary care provider, # visits/year)  | Survey, EHR                      |
| Other prior cancer screening (colonoscopy, mammogram)                 | Survey, EHR                      |
| Understanding of LDCT results (patient report vs. radiologist report) | Survey, EHR                      |

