| Perception of “being informed” about LDCT results (Likert scale)      | Survey              |
| Perception of “being informed” about follow-up plan (Likert scale)    | Survey                           |
| Perceived risk of lung cancer                                         | Survey              |
| Distress associated with LDCT results (Impact of Event Scale [IES])   | Survey          |
| Quality of communication with provider (Consultation Care Measure)    | Survey          |
| Patient adherence to provider-ordered follow-up (±30 days of date)    | Survey, Primordial  |

Lung-RADS score from their index LDCT (e.g. 12 months after Lung-RADS 1 or 2; 6 months for Lung-RADS 3).

**C.5.d. Outcome, predictors and covariates** (Table 1): Primary outcome: Adherence to recommendations for follow-up (including LDCT at appropriate interval), defined by Primordial and EHR review (if obtained at UW) or patient report (if not at UW).

**C.5.e. Analysis:** To determine whether patient adherence (yes/no) to follow-up study (as ordered by the provider) after LDCT differs by patient characteristics and understanding of LDCT results, chi-squared tests will be used to compare categorical variables (such as sex, race/ethnicity, insurance, income, smoking status), t-tests for continuous approximately normally distributed variables (such as age) and Wilcoxon rank-sum tests for non-normally distributed variables (such as pack-years of smoking). Understanding of LDCT (e.g. nodule yes/no) and follow up plan will be dichotomized as good vs. poor. We will evaluate patient's self-assessments of being informed as well as understanding of findings defined by comparing patient-report of results to radiologist report in the EHR. Patient characteristics associated at  $p < 0.1$  will be assessed in multivariable logistic regression models, adjusting for potential covariates and confounders to determine independent associations. Collinearity will be assessed using Variance Inflation Factors. Potential effect modification (e.g. education, quality of communication with provider) will be assessed by interaction terms and stratification.

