**C.5.f. Sample size:** We will survey patients who have been screened in the 6-15 months prior to the start of the award, and will continue to administer surveys over the first 18 months. In the past 2 years, referrals have grown substantially with 505 patients initiating LCS in 2016 and 2017. We anticipate mailings to ~500 patients, a 40-50% response rate, a range in the primary exposure of 30-60% (poor understanding of LCS results) and a 20-40% range in non-adherence from our preliminary data. Conservatively estimating 200 respondents, we have 80% power to detect an odds ratio of 2.25. This sample size is comparable or larger than studies of incidentally detected nodules that found significant associations.

**Aim 2. Explore patient understanding and preferences regarding the methods and information that providers should include in order to communicate the results of LCS in a focus-group based study.**

**C.6.a. Rationale:** There are limited published studies (primarily on incidental nodules) that consider a patient's: 1) understanding of LCS results, and 2) preferences for methods to communicate LCS results. A qualitative approach is particularly appropriate for identifying and describing beliefs and issues that have not been previously examined, and avoids assumptions that could prove to be incorrect if we were to only administer surveys in which items are necessarily constrained and feedback is limited. Patients will form the initial groups, but final groups will include primary care providers to engage in dialogue and obtain feedback.

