#### C.10. Table 4: Timeline and Milestones by Specific Aim over the 2-year funding period

|              |                                                                                                                                                                                                                                                                                                                                                                                                                                                                                                            |
|--------------|------------------------------------------------------------------------------------------------------------------------------------------------------------------------------------------------------------------------------------------------------------------------------------------------------------------------------------------------------------------------------------------------------------------------------------------------------------------------------------------------------------|
| Aim 1 | Month 1-2: Finalize surveys & obtain IRB approvals for all Aims; use Primordial to identify patients; Months 2-18: administer surveys to patients who have previously undergone LCS; Conduct interim analyses of data obtained by month 8 to inform Aim 3, with final analyses of all data conducted in months 18-21. Anticipated manuscripts: 1) Patient understanding and distress associated with LCS results in a real-world setting; 2) Patient characteristics associated with poor adherence to LCS |
| Aim 2 | Months 1-5: Recruit participants and conduct focus groups; Month 6-7: transcription, coding, and analysis of qualitative interviews. Anticipated manuscripts: 1) Patient preferences for reporting and understanding of LCS results                                                                                                                                                                                                                                                                        |

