| Aim 3 | Months 6-8: Finalize LCS reports & surveys; Months 9-21: Randomize patients, collect surveys; Months 21-24: clean & analyze data. Anticipated manuscripts: 1) Patient-oriented outcomes associated with LCS report; 2) Implementation assessment                                                                                                                                                                                                                                                           |

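### Aim 1 measures understanding after adherence is settled, so the H1a association may be biased in either direction and cannot show that poor understanding came first

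*Protocol*

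**What the plan says.** Aim 1 is a single survey; C.5.b declares "This is a cross-sectional study". C.5.c fixes when it is sent: "Participants will complete surveys 1-2 months after their planned follow-up per the" "Lung-RADS score from their index LDCT (e.g. 12 months after Lung-RADS 1 or 2; 6 months for Lung-RADS 3"). In Table 1 the exposure is "Understanding of LDCT results (patient report vs. radiologist report") and the outcome is "Patient adherence to provider-ordered follow-up (±30 days of date"). The same survey collects distress and quality of communication. C.5.e scores understanding against the radiologist's report in the EHR without naming which scan.

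On recruitment, C.5.f says "We will survey patients who have been screened in the 6-15 months prior to the start of the award", with surveys continuing over the first 18 months. C.10 Table 4 gives "Months 2-18: administer surveys to patients who have previously undergone LCS" for Aim 1, with an interim analysis of data to month 8, and "Months 9-21: Randomize patients, collect surveys" for Aim 3. Aim 3 is to randomise all patients screened at UW (C.7.f), stratified by initial versus follow-up screening (C.7.c), so rescans are included. H1a itself predicts only an association between poor understanding and lower adherence.

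**The concern.** The exposure is measured after the outcome, and the outcome can alter the exposure. A patient who returns to UW on time will usually have had a second LDCT and a second results letter before answering. A Lung-RADS 1 or 2 patient who did not return is recalling a letter about 13 to 14 months old. If the latest scan is scored, returning patients have had fresher information. If the index scan is scored, some of them may describe the newer scan and be marked wrong. Either choice treats the two outcome groups differently.

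From month 9 a second mechanism is added: patients rescanned at UW receive an Aim 3 letter, and about half get a report designed to improve understanding. Nothing in the protocol flags those patients within Aim 1.

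At stake is how H1a is read. C.5.f calls poor understanding the primary exposure, C.3 looks to Aim 1 for modifiable factors, and the month-8 results are meant to inform Aim 3. Those uses assume that understanding came before adherence.

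**Working it through.** **1. The protocol's own figure.** Inputs from C.5.f: 200 respondents, poor understanding 30-60%, non-adherence 20-40%, odds ratio 2.25, power 80%. Two-sided alpha 0.05 is assumed; it is stated only for Aim 3 (C.7.f). At mid-range, 45% exposed gives 90 versus 110 patients. With non-adherence 0.30 in the unexposed, the exposed rate is 2.25×0.30/(0.70+2.25×0.30) = 0.491. A two-proportion test with pooled variance has power 0.790, so the stated 80% reproduces at mid-range (0.66 to 0.81 across the stated ranges). An odds ratio of 2.25 is the yardstick for what follows.

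**2. Order of events.** Take the due date as D. The adherence window closes at D + 30 days; the survey is completed at D + 1 to 2 months. Exposure is recorded at or after closure of the outcome, and no earlier measurement is planned.

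**3. Aim 3 overlap alone, no true association.** Inputs from C.7.f: poor understanding 45% under usual care and 25% with the new report (the upper end of its 20-25%), balanced arms.
- Affected adherers: 0.5×45% + 0.5×25% = 35% poor understanding; non-adherers stay at 45%.
- Odds ratio in affected surveys: (0.45/0.55)/(0.35/0.65) = 1.52.
- Pooled, with a share f affected, adherers have 0.45 − 0.10f. At f = 0.55 (an assumption of roughly even mailing) this is 0.395, and (0.45/0.55)/(0.395/0.605) = 1.25. At f = 0.25 it is 0.425 and the odds ratio is 1.11.
- At 200 respondents and 30% non-adherence (60 versus 140), 45% versus 39.5% reaches p<0.05 about 11% of the time.

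**4. Ordinary second letter, no true association.** The documents give no size for this. Suppose a fraction c of poorly informed adherers become well informed after the second scan and letter. Adherers then have 0.45(1−c) poor understanding. With 60 versus 140 patients:
- c = 10%: 0.405, odds ratio 1.20, rejection probability 0.09
- c = 20%: 0.360, odds ratio 1.45, rejection probability 0.22
- c = 30%: 0.315, odds ratio 1.78, rejection probability 0.45
- c = 40%: 0.270, odds ratio 2.21, rejection probability 0.70

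An odds ratio of 2.25 needs c of about 41%.

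**5. The opposite direction.** Suppose the true odds ratio is 2.25, overall non-adherence is 30% and poor understanding is 45%. The non-adherence rates are then 0.224 (unexposed) and 0.394 (exposed). Among adherers the good-to-poor ratio is (0.55×0.776)/(0.45×0.606) = 1.56. If 20% of well-informed adherers describe the newer scan and are scored against the index scan, the observed odds ratio is 2.25×0.8/(1+0.2×1.56) = 1.37.

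**6. Timing rule against sampling window** (award start = month 0).
- A Lung-RADS 1 or 2 scan at month −15 was due at month −3. A survey at month 2 is 5 months past due.
- A Lung-RADS 3 scan at month −15 was due at month −9. A survey at month 2 is 11 months past due.
- To be no more than 2 months past due at month 2, the due date must be month 0 or later. That requires a Lung-RADS 1 or 2 scan at month −12 or later. For Lung-RADS 3, only scans at month −6, the very edge of the window, comply.

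**The case against.** The strongest reply is that the protocol claims only an association, in a study it openly calls cross-sectional, and recruits already-screened patients to fit a two-year award. That stands. A reader might infer that H1a cannot be answered at all; the documents do not support this, because an association can be estimated. What is lost is temporal order and confidence in its size.

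The Aim 3 part also has limits. Lung-RADS 1 or 2 patients in the named window fall due between months −3 and 6, so their surveys are due by month 8, before Aim 3 starts. Only later mailings can be affected, and the 55% share ignores this backlog. The month-8 data are free of Aim 3, though not of the ordinary second letter. It is also tempting to say that non-adherent patients never receive an Aim 3 letter. That is too strong: someone rescanned on day 35 is non-adherent yet may have a new letter before the survey. Nor does every adherent patient have a second LDCT letter, since follow-up may be other testing or take place outside UW.

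Finally, the survey was still to be finalised in months 1-2, and its wording or the SAP may name the scan and flag Aim 3 recipients. That could reduce the bias, but it would not undo the survey timing and overlap that the protocol itself fixes.

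**Conclusion.** The point holds for H1a. Understanding, distress and communication quality are recorded when adherence is essentially settled, the scored scan is not named, and Aim 1 mailing overlaps Aim 3 in months 9-18. The resulting association may be inflated or diluted and cannot establish that poor understanding came first.

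Under no true association, the Aim 3 overlap contributes an odds ratio of about 1.5 in affected surveys and about 1.25 pooled at an assumed 55% share. This rests on the protocol's 45% versus 25% contrast, balanced arms and unchanged understanding in non-adherers. The second-letter effect runs through all of Aim 1. Its size is unknown: 1.20 to 2.21 for an assumed 10% to 40% corrected, while confusion between scans could shrink a true 2.25 to about 1.37.

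The conclusion does not extend to H1b, since race, socioeconomic status and smoking are not set by a results letter, and it is not a criticism of the randomised comparison in Aim 3. Separately, the 1-2 month rule cannot hold for the oldest patients in the sampling window.

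**What to change.** In C.5.c and C.5.e:

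- Tie the understanding, distress and communication items to the index LDCT, and score understanding against the index radiology report.
- Record the dates of any later scan and results letter received before the survey.
- For H1a, flag Aim 3 recipients. Omit those assigned the new report and keep those assigned the usual letter, weighted for the randomised half (weight 2 under balanced allocation). Excluding every Aim 3 recipient would be worse, because it would remove almost only adherers.
- Add a sensitivity analysis limited to surveys returned before Aim 3 starts.
- State the H1a conclusion as non-directional. Index-anchored items reduce the second-letter effect but do not remove it.
- Reconcile the 1-2 month rule in C.5.c with the 6-15 month window in C.5.f and the month-2 start in C.10. Analyse patients surveyed later than the rule allows as a separate sensitivity group.

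The cost is some item wording, two date fields, and lost precision from dropping about half of the Aim 3-affected surveys. The items and date fields must be settled before the first mailing.

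An option is to survey patients who are not yet due before their due date, taking adherence from Primordial and the EHR with a short card for follow-up outside UW. This restores the time order. Its downside is that the survey, the two-week postcard and the four-week second packet may act as reminders near the due date, perhaps most for poorly informed patients. It also cannot help those already past due.

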#### C.10. Table 4: Timeline and Milestones by Specific Aim over the 2-year funding period

|              |                                                                                                                                                                                                                                                                                                                                                                                                                                                                                                            |
|--------------|------------------------------------------------------------------------------------------------------------------------------------------------------------------------------------------------------------------------------------------------------------------------------------------------------------------------------------------------------------------------------------------------------------------------------------------------------------------------------------------------------------|
| Aim 1 | Month 1-2: Finalize surveys & obtain IRB approvals for all Aims; use Primordial to identify patients; Months 2-18: administer surveys to patients who have previously undergone LCS; Conduct interim analyses of data obtained by month 8 to inform Aim 3, with final analyses of all data conducted in months 18-21. Anticipated manuscripts: 1) Patient understanding and distress associated with LCS results in a real-world setting; 2) Patient characteristics associated with poor adherence to LCS |
| Aim 2 | Months 1-5: Recruit participants and conduct focus groups; Month 6-7: transcription, coding, and analysis of qualitative interviews. Anticipated manuscripts: 1) Patient preferences for reporting and understanding of LCS results                                                                                                                                                                                                                                                                        |
| Aim 3 | Months 6-8: Finalize LCS reports & surveys; Months 9-21: Randomize patients, collect surveys; Months 21-24: clean & analyze data. Anticipated manuscripts: 1) Patient-oriented outcomes associated with LCS report; 2) Implementation assessment                                                                                                                                                                                                                                                           |

## ASSURANCES

### (1) HUMAN SUBJECTS

#### Training and Certification in Human Subjects Research

All personnel will be required to provide written evidence documenting education in the protection of human subjects. Personnel who have not previously completed human subject training will be required to complete the CITI Basic Course in Human Subject Protections. This is an online self-paced course that proceeds in a stepwise fashion, module by module with the choice of either a biomedical or social/behavioral focus. The web address for this course is: <http://citiprogram.org>.

#### 1. Risks to the subjects

**1.a. Human subjects' involvement and characteristics:** For all aims, we will recruit patients from the primary care and pulmonary clinics affiliated with Harborview Medical Center (HMC), the University of Washington (UW) Medical Center (UWMC), and the Seattle Cancer Care Alliance (SCCA) Early Lung Cancer Detection and Prevention Clinic, all in Seattle, WA. We anticipate mailing surveys to approximately 500 participants with 200 respondents for Aim 1; enrolling 60-70 participants for Aim 2; and mailing surveys to approximately 430 participants with 160 respondents for Aim 3. Similar inclusion and exclusion criteria will be used for all aims. Inclusion criteria: 1) Completed lung cancer screening (LCS) with at least an initial low dose chest CT (LDCT), and 2) Able to give informed consent. Exclusion criteria: 1) Cognitive or language limitations (i.e., expressive language limitations, non-English speaking); or 2) Known malignancy other than non-melanoma skin cancer. We anticipate surveys will take approximately 20 minutes to complete. Focus groups will require approximately 70-90 minute. Patients will range in age, and demographic characteristics. No patients will be excluded based on demographic characteristics.

**1.b. Sources of materials:** Sources of data will include: 1) Electronic health record (EHR) and Primordial lung cancer registry database; 2) Surveys; 3) Digitally recorded focus group sessions or interviews; 4) Anonymous transcripts of focus groups.

**1.c. Potential risks:** The potential risks for harm from this research include those that may result from invasion of privacy, breach of confidentiality, distress or anxiety, and lost time. This study will be designed specifically to minimize risks to subjects. We will implement and strictly adhere to security measures designed to protect participant confidentiality and ensure data security.

EHR and Primordial database review: The primary risk associated with EHR and Primordial review is invasion of privacy and breach of confidentiality.

Surveys: The potential risks are minor, and are primarily related to the stress of completing surveys and the risk to privacy. Surveys are voluntary, and subjects are free to skip any questions they do not wish to answer. Subjects are informed in consent forms that completing the surveys may cause emotional distress by causing them to think about symptoms and conditions that are unpleasant.

Qualitative interviews are digitally recorded sessions: Participants will be made aware during the informed consent process that focus group sessions will be digitally recorded and that the nature of these group will involve participants speaking about LCS. No participant full names will be recorded on the tapes and the transcripts will be coded by participant number rather than name in order to protect participant confidentiality. Efforts will be made to minimize the burden of stress for all participants. During qualitative data collection, focus group leaders will assure participants that they can, at any time during the group, refuse to answer any question, and at any time elect to withdraw from the study. Further, they will assure participants that the data will be anonymous, and that their participation or lack thereof will not be reported to their peers or providers.

**1.d. Treatment alternatives:** No alternative. Participants may decline to partake in this study.

